## Abstract

Valproate is the most effective treatment for idiopathic generalised epilepsy. Currently, its use is restricted in women of childbearing potential owing to high teratogenicity. Recent evidence extended this risk to men’s offspring, prompting recommendations to restrict use in everybody aged <55 years. This study will evaluate mortality and morbidity risks associated with valproate withdrawal by emulating a hypothetical randomised-controlled trial (called a “target trial”) using retrospective observational data. The data will be drawn from ~250m mainly US patients in the TriNetX repository and ~60m UK patients in Clinical Practice Research Datalink (CPRD). These will be scanned for individuals aged 16–54 years with epilepsy and on valproate who either continued, switched to lamotrigine or levetiracetam, or discontinued valproate between 2014–2024, creating four groups. Randomisation to these groups will be emulated by baseline confounder adjustment using g-methods. Mortality and morbidity outcomes will be assessed and compared between groups over 1–10 years, employing time-to-first-event and recurrent events analyses. A causal prediction model will be developed from these data to aid in predicting the safest alternative antiseizure medications. Together, these findings will optimise informed decision-making about valproate withdrawal and alternative treatment selection, providing immediate and vital information for patients, clinicians and regulators.

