### Addressing Aim 1: Target trial emulation

#### Target trial design

A hypothetical target trial will be emulated in which young men and women taking valproate would be randomised to either continue valproate, switch to lamotrigine or levetiracetam, or discontinue valproate [21]. The following mortality and morbidity outcomes would be assessed over the subsequent five years:

Deaths (all-cause/epilepsy-related);ED/hospital admissions (all-cause/epilepsy-related);Seizures (symptom codes);Falls;Injuries;Burns;Aspiration pneumonia;Manic/bipolar episodes;New-onset depression;Self-harm/suicide;A composite morbidity index incorporating seizures, injuries, admissions, depression.

Intention-to-treat (ITT) and per-protocol effects would be assessed between groups [21]. Analysis would take a time-to-first-event approach (Cox-proportional hazards model) for deaths, new-onset depression and composite morbidity. A recurrent events approach (e.g., Prentice-Williams-Peterson Total Time Model) would be taken for the remaining outcomes.

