#### Target trial emulation using observational data from TriNetX and CPRD

*Eligibility criteria*. Anonymised, person-level, electronic health data will be extracted from TriNetX and CPRD, linked across primary care, ED, inpatients, outpatients, and mortality subsets. The study period will be from 01/01/2014 to 01/01/2024. Included will be men and women aged 16–54 years. The study will take an open cohort design with patients entering the cohort when the following criteria are met:

Either: ≥1 epilepsy disease or symptom code recorded during the study period and two separate valproate prescription instances over the preceding 12 months before at least one of the epilepsy disease or symptom codes;

Or: ≥1 epilepsy disease or symptom code recorded any time before the study period with at least two separate valproate prescription instances over 12 months during the study period.

TriNetX and CPRD use ICD-10-CM and SNOMED codes, respectively. The coding strategy combining disease and symptom codes with valproate, as used our published study successfully [20], was shown to accurately identify epilepsy cases in our prior work [28,29].

Treatment arms:

Withdrawn valproate and commenced lamotrigineWithdrawn valproate and commenced levetiracetamWithdrawn valproate and no new ASM commencedContinues valproate

*Treatment assignment*. Baseline (time 0) will be defined as when valproate dose reduction commences (treatment arms 1–3) or prescription of valproate at a matched time (arm 4). Eligible individuals are assigned at baseline to the treatment strategy that their data are consistent with [21]. To emulate randomisation, adjustment is made for baseline confounders using Robins’ generalised methods (g-methods, e.g., inverse probability weighting) [21], considering age, sex, ethnicity, deprivation, type of epilepsy (using G40 codes), baseline seizure frequency (symptom codes recorded over preceding 12 months), alcohol excess, developmental delay, Cambridge Multimorbidity Score, length of valproate treatment, valproate dose, and ASMs used other than valproate. The final set of covariates required to adjust for confounding will be chosen using a causal directed acyclic graph [21].

*Outcomes*. These are listed in the target trial design section and derived from our prior work [1,20,30,31], and public consultation. All coded events will be recorded for flexible categorical or continuous analyses, as needed.

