*Causal estimand*: Assesses impact of treatment arms 1–3 vs. 4 on outcome (per-protocol assumption as observational data limits ITT assessment) [21].

*Start and end of follow-up*. The start of follow-up (Time 0 or index date) will be defined as when valproate treatment discontinued (treatment arms 1–3) or prescription of valproate at a matched time (arm 4). For time-to-first-event analyses, the end of follow-up will be defined as when the outcome occurs, censoring (including deviation from assigned treatment or leaving the study catchment area), or 10 years. For recurrent events analyses, alongside censoring as above, the end of follow-up will be 10 years, allowing for all events to be assessed throughout follow-up.

*Statistical analysis*: mirrors target trial section.

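### The per-protocol analysis censors at treatment deviation but states adjustment for baseline confounders only, so the effect can be biased, in a direction the documents do not determine

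*Protocol article*

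**What the plan says.** All references are to the Protocol article.

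- **Estimand.** Arms 1–3 are compared with arm 4 under a "per-protocol assumption as observational data limits ITT assessment" (Causal estimand).
- **Censoring.** In time-to-first-event analyses, follow-up ends at the outcome or at "censoring (including deviation from assigned treatment or leaving the study catchment area), or 10 years". The recurrent-event rule is the same: "For recurrent events analyses, alongside censoring as above, the end of follow-up will be 10 years" (Start and end of follow-up).
- **Adjustment.** "To emulate randomisation, adjustment is made for baseline confounders using Robins’ generalised methods (g-methods, e.g., inverse probability weighting" (Treatment assignment). The Abstract agrees: "Randomisation to these groups will be emulated by baseline confounder adjustment using g-methods". Every covariate listed describes the patient at or before time 0. Seizures, for example, enter as "baseline seizure frequency (symptom codes recorded over preceding 12 months".
- **Models.** The statistical analysis is said to mirror the target trial section, which names a Cox model and, as an example, a Prentice-Williams-Peterson model. No censoring weight or post-baseline covariate is mentioned.
- **Hypothetical trial.** "Intention-to-treat (ITT) and per-protocol effects would be assessed between groups" (Target trial design).

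**The concern.** Adjustment for baseline confounders can support a comparison of the strategies that patients start at time 0. A per-protocol effect with artificial censoring needs something further: given what has been adjusted for, patients censored at deviation must be exchangeable with those who stay in follow-up. That is implausible here if only baseline variables are used. The Introduction reports that earlier withdrawal studies usually found relapse in generalised epilepsy. Relapse is a plausible reason to restart valproate or change antiseizure medication (ASM), and it also predicts later admissions, injuries and death. Patients would then leave follow-up when their risk has just changed, possibly at different rates across arms.

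The Aim 1 figures are meant for the risk section of a national decision support tool (Pathways to impact). A bias that readers cannot sign would be carried into individual treatment decisions.

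**Working it through.** **1. The plan's own figure.** The only related design figure is the minimum sample size of 881 (Table 1). With p1 = 2977/8021 = 0.3712 and p2 = 2471/8021 = 0.3081:

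n = (1.960 + 0.842)² × [0.3712 × 0.6288 + 0.3081 × 0.6919] / (0.3712 − 0.3081)² = 880.7 with unrounded inputs, which rounds up to 881.

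It reproduces. The formula contains no follow-up or censoring term, so this point does not change it.

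**2. Two-state illustration.** None of these inputs is in the documents. Patients are stable or relapsed, in monthly steps over 60 months. Relapse is 2% per month in the withdrawn arm and 0.8% in the continuing arm. The outcome hazard is h0 = 0.05/12 per month while stable and k × h0 after relapse. Each month:

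- events = h0 × (stable) + k × h0 × (relapsed)
- those remaining are then censored with probability c0 (stable) or c1 (relapsed)
- annual rate = 12 × total events / total person-months

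The true rate ratio sets c0 = c1 = 0. It is 0.0696/0.0594 = 1.17 for k = 2 and 0.0872/0.0677 = 1.29 for k = 3. With censoring at deviation and no weights:

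| c1 per month, withdrawn / continuing | k = 2 (true 1.17) | k = 3 (true 1.29) |
|---|---|---|
| 10% / none | 0.0575/0.0594 = 0.97 | 0.0646/0.0677 = 0.95 |
| 5% / none | 0.0613/0.0594 = 1.03 | 0.0717/0.0677 = 1.06 |
| 10% / 10% | 0.0575/0.0532 = 1.08 | 0.0646/0.0562 = 1.15 |
| 3% / 10% | 0.0639/0.0532 = 1.20 | 0.0766/0.0562 = 1.36 |
| 1% / 10% | 0.0675/0.0532 = 1.27 | 0.0833/0.0562 = 1.48 |
| 1% / 1%, unrelated to relapse | 0.0680/0.0586 = 1.16 | 0.0842/0.0661 = 1.27 |

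c0 is 0.2% per month, except none in the continuing arm in the first two rows and 1% in both arms in the last row.

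**3. Does the remedy work?** The first row was simulated with 300,000 patients per arm, weighting each patient by 1/∏(1 − c) according to post-baseline relapse. The unweighted ratios of 0.97 and 0.95 became 1.18 and 1.28, against true values of 1.17 and 1.29. These weights used the known deviation probabilities; in practice they would be estimated.

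**4. A second model.** This one uses a shared gamma frailty (variance 0.5 to 2) over 5 years. The ED hazard is 0.083 per year, from Table 1's 5,448 events in 16,042 patients: −ln(1 − 0.3396)/5 = 0.083. The rest is assumed: 0.3 seizures per year, with 20% or 50% of seizures in the withdrawn arm followed by return to valproate.

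- Continuing arm deviating at random, 5% per year: a null effect appears as HR 0.73–0.95. A conditional HR of 1.3 (1.20–1.28 with full follow-up) appears as 0.90–1.22.
- Continuing arm with the same seizure-driven deviation: the null is 0.99–1.01, and 1.3 appears as 1.23–1.27, so there is almost no bias.
- Continuing arm deviating twice as fast: estimates move upwards and harm is overstated.

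Both models show that the bias can be material. They also show that its sign depends on deviation in the continuing arm, about which the documents give no figure.

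**The case against.** The strongest reply is that this is an argument from silence. The article is condensed and no analysis plan is shown. It names g-methods, which can handle time-varying covariates, gives inverse probability weighting only as an example, and leaves the final covariates to a causal graph. This stands in part: nothing excludes censoring weights. But the article does fix the estimand, the censoring rule and the purpose of the g-methods, and it ties that purpose to baseline confounders in two places. Followed as written, these choices do not fit together.

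Four stronger readings are tempting, and the documents do not support them.

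- **That harm is understated.** This assumes that relapse-driven deviation dominates in the withdrawn arms. Uncontrolled seizures on valproate could also prompt a treatment change, and the tables above then reverse.
- **That a harmful withdrawal would look neutral or protective.** In the frailty model, only one of six harmful scenarios falls below 1, at the extreme corner (variance 2, 50% return). That model is also unadjusted, whereas the plan adjusts for baseline seizure frequency, epilepsy type and other ASMs.
- **That all outcomes are equally affected.** In the first-event composite, a coded seizure ends follow-up before any return to valproate.
- **That the intention-to-treat (ITT) statements strictly contradict each other.** Target trial design describes the hypothetical trial, and the emulation openly departs from it. The statement that the analysis mirrors that section can be read as covering the models only.

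**Conclusion.** The point holds as a mismatch between the estimand and censoring rule on one side and the stated adjustment on the other. Censoring at deviation with baseline adjustment alone does not identify the per-protocol effect if post-baseline events drive both deviation and outcome, which is plausible here.

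The direction is not determined. Harm is understated if relapse-driven return to valproate dominates in the withdrawn arms, and overstated if relapse-driven deviation is sufficiently faster in the continuing arm. With similar deviation in both arms, one model shows moderate understatement (1.17 to 1.08) and the other almost no bias. Deaths, depression and recurrent outcomes are most exposed. Every ratio rests on assumed relapse and deviation rates and shows only that the bias can matter.

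The plan also sets aside the ITT analogue, which is the comparison its baseline adjustment is suited to. That analogue is usable only if the arms can be told apart at time 0, and this is not yet secured: Treatment assignment places time 0 at the start of dose reduction, while Start and end of follow-up places it at discontinuation.

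**What to change.** 1. Under Start and end of follow-up, state that censoring at deviation is handled with stabilised inverse-probability-of-censoring weights or the parametric g-formula. Use time-updated codes for seizures, ED visits, admissions, mood episodes and ASM changes. Combine the censoring weights with the baseline treatment weights in both the Cox and the recurrent-event models.
2. Report, at least as a sensitivity analysis, the observational analogue of ITT: groups by strategy assigned at time 0, with no censoring at later treatment change. Reword the statement that observational data limit ITT.
3. Reconcile the two time 0 definitions so that the arms can be distinguished at the chosen point.

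**Cost.** More analysis work and some loss of precision from the weights. The article already plans to record all coded events and data access is still being sought, so the time-updated variables can be included in the extraction from the outset. The sample size figure of 881 is unaffected.

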### Addressing Aim 2: Causal prediction modelling

A causal prediction model will be created using Cox-proportional hazards of time-to-first-event in a causal framework [26]. The predicted outcome will be a composite personal harms risk combining epilepsy-related deaths, seizures, injuries, admissions, and depression. Predictors for definite inclusion in the final model will be treatment arms 1–4. Candidate predictors considered in addition will be taken from the list of baseline confounders adjusted in the target trial emulation, alongside any additional variables considered to influence outcome but not treatment assignment. *A priori* clinical expertise and data-driven variable selection will refine the predictor variable list for modelling [30]. Penalisation methods (e.g., *lasso*), will be used to combine variable selection with shrinkage (reducing overfitting risks).

The model will be developed in TriNetX to help ensure it is internationally generalisable [32]. External validation will be undertaken in CPRD, facilitating subsequent clinical implementation [32]. Internal validation within TriNetX will involve 1,000 bootstrap analysis samples. Nagelkerke’s R^2^ and Brier Scores will estimate overall model performance. Calibration will be estimated with calibration-in-the-large, calibration slope, and flexible calibration plots, and discrimination with C-index. Calibration and discrimination will be reassessed within CRPD to externally validate model performance [32]. Counterfactual prediction will be embedded into the model development [26], allowing patients and clinicians to answer clinically meaningful questions such as “at the point of proposed valproate withdrawal, accounting for baseline characteristics, what is the risk of epilepsy-related death or composite morbidity for levetiracetam? And what is it for lamotrigine?”

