### Aims

Identify whether there are any differences in mortality or morbidity outcomes between remaining on valproate compared with valproate withdrawal and switch to lamotrigine, levetiracetam, or no new ASM.Develop and validate a causal prediction model that clinicians and patients could use when planning to withdraw from valproate to predict which of these alternative ASMs would have the lowest mortality and morbidity, taking baseline clinical and demographic characteristics into account.

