### Hypotheses

Some morbidity or mortality outcomes will be increased when valproate is withdrawn, regardless of whether switched to lamotrigine, levetiracetam, or no new ASM;The causal prediction model developed will be able to predict which alternative ASMs are safest.

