### Benefits to PWE

This study will benefit PWE as substantial numbers of young men and women may soon be invited by their clinicians to come off valproate owing to both current and new regulatory changes [5,6]. Whilst this is justified in terms of preventing teratogenic harm, the patients will wish to know what the risks of withdrawing from valproate are for their own health [24,25]. This study will provide immediate evidence to help doctors answer that question [10]. It will also help patients make safer decisions over switching to alternative ASMs by generating the first ever causal prediction tool for this purpose [26]. This will be the largest study of valproate withdrawal to date, the first to assess risks in men and first to assess multiple outcomes beyond seizures alone for both men and women [11–17]. These outcomes will be collaboratively chosen with PWE through public engagement strategies, ensuring their relevance and impact on those most affected. Finally, mortality prediction is highlighted as a key recommendation for epilepsy research by NICE [27], meaning the causal prediction model generated by this study also addresses an established research need for PWE.

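### The Aim 2 tool is said to predict the option with the lowest mortality, but its single first-event composite gives no mortality risk

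*Protocol article*

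**What the plan says.** The section on Aim 2 specifies the model and its outcome: "A causal prediction model will be created using Cox-proportional hazards of time-to-first-event in a causal framework", and "The predicted outcome will be a composite personal harms risk combining epilepsy-related deaths, seizures, injuries, admissions, and depression". It states no separate death model, competing-risk model or multistate model.

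The follow-up rule, written for Aim 1, reads: "For time-to-first-event analyses, the end of follow-up will be defined as when the outcome occurs". This is also what a first-event analysis means in general, so it describes the Aim 2 model as well.

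Three statements say what the tool will deliver:
- Aims: clinicians and patients could use it "to predict which of these alternative ASMs would have the lowest mortality and morbidity".
- Hypotheses: "The causal prediction model developed will be able to predict which alternative ASMs are safest".
- Benefits to PWE: "mortality prediction is highlighted as a key recommendation for epilepsy research by NICE", "meaning the causal prediction model generated by this study also addresses an established research need for PWE".

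Aim 1 is different. Its outcome list in the Target trial design section has "Deaths (all-cause/epilepsy-related") as an item of its own, separate from a morbidity composite that contains no deaths. Pathways to impact plans to put Aim 1 figures into the national decision aid beside a link to the tool, and also to place an interactive version of the model in a public online repository.

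**The concern.** The use of a composite is not in question. The issue is what a tool built on this composite can claim. Two groups of deaths do not count as deaths in the model: those after a first seizure, injury, admission or depression code, and those not classed as epilepsy-related. The deaths that do count are merged with far commoner non-fatal events, so a mortality risk cannot be recovered from the output.

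Someone using the online tool to compare lamotrigine with levetiracetam would see a difference in composite risk. If they take it as the mortality prediction that the Aims and Benefits sections describe, they rely on something the model does not estimate.

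**Working it through.** **Claims against specification.** This part needs no assumed rate.

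| Statement | What it needs | What the Aim 2 model gives |
|---|---|---|
| Lowest mortality and morbidity (Aims) | Risk of death by arm | Risk of any component by arm |
| Safest alternative (Hypotheses) | Depends on the meaning of safest | Enough only if it means composite harm |
| Mortality-prediction need (Benefits to PWE) | Individual risk of death | None |

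**The plan's own figures.** Table 1 sizes the prediction model on emergency department attendance: 5,448/16,042 = 0.3396, and 0.3396/5 = 0.068 a year. With 20 parameters, shrinkage 0.9 and 15% of the maximum Cox-Snell R²:
- maximum R² = 1 − exp{2[0.34 ln(0.068) − 0.34]} = 0.9186
- R² = 0.15 × 0.9186 = 0.1378
- n = 20/[(0.9 − 1) ln(1 − 0.1378/0.9)] = 1,204, as stated.

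The arithmetic is right, and the point does not depend on it.

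**Illustration of size.** The documents give neither a death rate nor a composite rate. Assume constant, independent hazards.
- Non-fatal rate h: 0.068 a year (Table 1, emergency attendance alone, used as a floor); 0.139 (50% by 5 years, assumed); 0.322 (80% by 5 years, assumed).
- Epilepsy-related death rate d: 0.001 to 0.003 a year (assumed), with 0.01 as a high value.

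Formulas:
- Share of first events that are deaths: d/(d + h).
- Hazard ratio for the composite if one arm doubles d and leaves h unchanged: (h + 2d)/(h + d).
- Share of 5-year epilepsy-related deaths that follow a non-fatal event: 1 − [d/(d + h)][1 − exp(−5(d + h))]/[1 − exp(−5d)].

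| h | Share, d = 0.001 to 0.003 | HR, same d | Share, d = 0.01 | HR, d = 0.01 | Deaths after a non-fatal event |
|---|---|---|---|---|---|
| 0.068 | 1.4-4.2% | 1.014-1.042 | 12.8% | 1.128 | 15% |
| 0.139 | 0.7-2.1% | 1.007-1.021 | 6.7% | 1.067 | 28% |
| 0.322 | 0.3-0.9% | 1.003-1.009 | 3.0% | 1.030 | 50% |

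**Set against precision.** The approximate 95% factor for lamotrigine versus levetiracetam is exp(1.96 × √(2/events per arm)), with events per arm = n × [1 − exp(−5(h + d))]. The split over three withdrawal arms is assumed equal, with full 5-year follow-up.
- n = 14,234/9 = 1,582 (a third of the pilot cohort withdrawn): factor 1.08-1.14.
- n = 8,021/3 = 2,674 (the withdrawn group in Table 1): factor 1.06-1.10.

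At d up to 0.003 the shift from a doubling is smaller than either factor at every h. At d = 0.01 and h = 0.068 the HR of 1.128 is just inside 1.130 for the smaller arms, but outside 1.10 for the larger.

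**The case against.** The strongest reply is that the Aims sentence names mortality and morbidity together, and that the composite, which includes epilepsy-related death, puts that joint quantity into practice. Under this reading only the Benefits section clearly claims mortality prediction. That softens the conflict with the Aims but does not remove it: a composite that omits other deaths, and any death after a first non-fatal event, does not show which drug has the lowest mortality.

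The example question at the end of the Aim 2 section asks about epilepsy-related death or composite morbidity. It could hint at a second, separate output. It is more naturally read as the composite itself, whose parts it matches, and no other outcome is specified. It is not a further error.

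Aim 1 does estimate all-cause and epilepsy-related deaths, and its figures are meant for the national decision aid. This deserves credit. But these are contrasts between arms, not the prediction claimed for the model, and nothing says that they appear in the standalone online version.

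Three stronger readings are tempting, and the documents do not support them.
- A reader might infer that users will be told which drug is safest. The protocol describes a risk for each drug; the word safest stands in a hypothesis, not in a description of the display.
- A reader might infer that the tool would rank a deadlier drug as better. That is unknown. The protocol calls emergency attendance a good predictor of mortality, so fatal and non-fatal harm may move together, and the doubling with h unchanged is a worst case for the composite.
- A reader might infer that any mortality difference would be lost in the noise. That holds at the lower assumed rates, but not generally, as the case at 1% a year with the larger arms shows.

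**Conclusion.** The point holds as a mismatch within the article between what the Aim 2 tool is said to predict and the one outcome specified for it. It follows from the outcome definition alone. A fuller analysis plan would not normally settle it, because both the claims and the outcome are stated outright.

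The size is illustrative only. It rests on assumed death rates, assumed upper non-fatal rates, and constant independent hazards. At 0.1-0.3% a year, deaths are about 0.3-4% of first events and a doubling moves the composite hazard ratio to at most about 1.04. At 1% a year the share is 3-13% and the ratio 1.03-1.13. Across this range at least about 87% of first events are non-fatal, so morbidity will probably drive the ranking. No sample size is affected.

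**What to change.** 1. In Aims, Hypotheses and Benefits to PWE, limit the claims for the model to composite harm.
2. In the Aim 2 section, state that the tool, including the standalone online version, shows the Aim 1 all-cause and epilepsy-related mortality estimates by arm, with confidence intervals, beside the composite risk.
3. State there that the composite alone is not presented as a mortality ranking.

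The cost is narrower claims and a little more reporting. Aim 1 contrasts arms 1-3 with arm 4, so absolute risks by arm need weighted survival curves from the same analyses.

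The mortality figures will be imprecise. With 1,582 patients per arm and full 5-year follow-up (both assumed), deaths per arm are 1,582 × [1 − exp(−5d)]:
- Epilepsy-related, 0.1-0.2% a year: 8 to 16 deaths, a 5-year risk of 0.5% (95% CI 0.2-1.0%) to 1.0% (0.6-1.6%).
- All-cause, 0.5-1% a year (assumed): 39 to 77 deaths, 2.5% (1.8-3.4%) to 4.9% (3.9-6.1%).

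Censoring and weighting widen these. They may not separate lamotrigine from levetiracetam, but they show the user how little is known about mortality. A separate death model, with follow-up continued past non-fatal events and fewer predictors, is optional and worthwhile only if deaths are numerous enough.

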### Sample size calculation

See Table 1.

**Table 1 pone.0306226.t001:** Sample size calculation.

Outcome: Emergency department attendance (a global measure of morbidity and a good predictor of mortality) Data source: Mbizvo *et al*. [20]			
**Target trial emulation phase**		**Prediction model phase**	
**Method**	# Proportions from the pilot study p1 <- 2977 / 8021 # valproate withdrawn group p2 <- 2471 / 8021 # group remaining on valproate # Set significance level and power alpha <- 0.05 power <- 0.80 # Z-values for two-tailed test z_alpha <- qnorm(1—alpha / 2) z_power <- qnorm(power) # Calculate sample size n <- ceiling((z_alpha + z_power)^2 * ((p1 * (1—p1)) + (p2 * (1—p2))) / (p1—p2)^2) # Display the result cat("Sample size needed for the target trial emulation study:", n, "\n")	**Method**	Sample size criteria from our previous work for developing a time-to-event prediction model to estimate the minimum required sample size for our model development are used [33].
**Result**	The minimum sample size in the target trial emulation study is 881.	**Assumptions**	
		**(i)**	We target an overall shrinkage factor of 0.9.
		**(ii)**	We assume the outcome rate to be 0.068, calculated using the 5,448 events that occurred out of 16,042 patients within the pilot study, with a median survival time of 5 years.
		**(iii)**	The performance of the model would achieve 15% of the maximum possible cox-snell R-squared for the given outcome rate.
		**(iv)**	We would consider 20 candidate predictor parameters within the model development process.

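### The Aim 2 Cox model names no arm-by-covariate terms and budgets for about one at most, so as listed it ranks the alternatives identically for every patient; nor are its confounders protected from lasso selection

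*Protocol article*

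**What the plan says.** The Aims section sets the task for the model: "to predict which of these alternative ASMs would have the lowest mortality and morbidity, taking baseline clinical and demographic characteristics into account". The matching hypothesis is "The causal prediction model developed will be able to predict which alternative ASMs are safest".

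The section on Aim 2 gives the model type: "A causal prediction model will be created using Cox-proportional hazards of time-to-first-event in a causal framework". It then names the predictors in two groups. The first is fixed: "Predictors for definite inclusion in the final model will be treatment arms 1–4". The second is optional: "Candidate predictors considered in addition will be taken from the list of baseline confounders adjusted in the target trial emulation", together with variables thought to affect outcome but not treatment assignment. Clinical judgement and data-driven selection then refine this list, and penalisation such as lasso "will be used to combine variable selection with shrinkage". The section adds that counterfactual prediction will be built in. Its example question asks for one patient's risk on levetiracetam and on lamotrigine.

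Table 1 fixes the size of the model: "We would consider 20 candidate predictor parameters within the model development process". The minimum sample for development is given as 1,204. The Treatment assignment paragraph under Aim 1 lists 12 baseline confounders and leaves the final set to a causal graph.

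**The concern.** Aim 2 asks which alternative carries the lowest risk once a patient's own characteristics are considered. Those characteristics can change the answer only if the effect of arm on the hazard is allowed to differ between patients. Nothing in the two predictor groups does this, and the parameter budget looks like that of a model with arm and covariates entered side by side.

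A second weakness concerns the drug contrasts themselves. Confounders enter only as candidates, and lasso keeps variables according to how well they predict outcome. A variable that strongly predicts treatment but only weakly predicts outcome can be dropped, and the comparison of arms is then confounded.

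The planned performance measures (Nagelkerke's R², Brier score, calibration measures, C-index) describe risk prediction overall. None is stated by arm, so a model could score well on all of them while its between-drug contrasts were wrong. The tool is to be placed online, with a link proposed for the NHS England decision support tool. Readers could take one common ranking for advice tailored to them.

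**Working it through.** **1. Reproduce the plan's 1,204.** Inputs from Table 1: shrinkage S = 0.9, outcome rate 0.068 per year (5,448 / 16,042 / 5 = 0.0679), 5 years, R² at 15% of its maximum, P = 20 parameters.

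- Events per patient: E = 0.068 × 5 = 0.34.
- Null log-likelihood per patient: E·ln(rate) − E = 0.34 × ln(0.068) − 0.34 = −1.254.
- Maximum R² = 1 − exp(2 × −1.254) = 0.9186; 15% of this is 0.1378.
- n = P / [(S − 1)·ln(1 − R²/S)] = 20 / [(−0.1) × ln(1 − 0.1378/0.9)] = 1,203.6, rounded up to 1,204.

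The figure reproduces at P = 20. Each parameter costs 1,203.6 / 20 = 60.18 patients.

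**2. Count the parameters.** Four arms need 3 terms. The 12 listed confounders are age, sex, ethnicity, deprivation, epilepsy type, baseline seizure frequency, alcohol excess, developmental delay, multimorbidity score, length of valproate treatment, valproate dose and other ASMs. At one parameter each, 3 + 12 = 15, which leaves 5. An interaction of arm with a one-parameter covariate costs 3, so one fits and two (6) do not. Ethnicity, epilepsy type and other ASMs would normally need several parameters each, and extra prognostic variables are also allowed. Both reduce the space further.

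**3. Ranking without interactions.** For arm a and covariates x,

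risk(a, x) = 1 − exp{−H₀(t)·exp(b_a + g′x)}.

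For any fixed x this rises with b_a, so the order of the arms is the order of the b_a whatever x is. As a check, 10,000 simulated patients with assumed coefficients gave 1 distinct ranking of arms 1–3 under this model and 3 rankings once a single arm-by-covariate term was added. Without interactions the absolute risks still varied widely: arm 1 risk ran from about 7% to 85%, and the difference between arms 2 and 1 from about 1 to 5.5 percentage points (5th to 95th percentile). The coefficients are illustrative; the constant order is algebra.

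**4. Cost of adding interactions under the same criterion (S and R² unchanged).**

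| Model | Parameters | Minimum n |
|---|---|---|
| As budgeted | 20 | 1,204 |
| 3 arm + 12 covariates + arm by 4 covariates (12) | 27 | 27 × 60.18 → 1,625 |
| 3 arm + 12 covariates + arm by all 12 (36) | 51 | 3,070 |
| 3 arm + 17 covariates + arm by all 17 (51) | 71 | 4,273 |

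Table 1 puts the TriNetX sample at about 14,234, with around a third withdrawn: 14,234 / 3 ≈ 4,745, split over arms 1–3 in proportions that are not given.

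**The case against.** The strongest reply is that the article never says the model is confined to main effects. It lists candidate variables, not the functional form. Its commitment to counterfactual prediction, and its use of clinical judgement in refining predictors, leave room for effect modification that an analysis plan may spell out. This stands as far as it goes: a reader might infer that interactions are excluded, and the text does not support that. What remains is that the listed content and the published parameter count describe a model with little room for them. That count is a stated figure, not silence.

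It may also be said that the budget could hold interactions. One fits at 15 main-effect parameters, and more would fit if the causal graph or clinical refinement shortened the candidate list. That is correct, so the budget is tight and does not make interactions impossible.

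A reader might go further and conclude that Aim 2 cannot be answered at all. That is too strong. Without interactions the model still gives patient-specific risks under each arm, which answers the section's own example question. It also identifies one lowest-risk alternative overall, which speaks to the hypothesis as worded.

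On lasso, the arms are guaranteed a place, so they cannot be selected out; whether they would be shrunk is not stated. Dropping a confounder biases the contrasts only if confounding is not handled in another way. The Aim 1 weights would do this, and nothing rules them out for Aim 2. The section does not say they are used, so the risk is conditional but open.

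**Conclusion.** The point holds in this form: followed as listed and budgeted, the model individualises absolute risk but not the choice between alternatives, and its causal contrasts are not protected from confounder selection. The size of the first part is exact for a Cox model without arm-by-covariate terms: every patient receives the same ordering of lamotrigine, levetiracetam and no new ASM. It rests on reading the predictor list and the 20-parameter budget as the intended model. The second part has no number; it depends on lasso dropping a relevant confounder and on the Aim 1 weights not being carried over.

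The sample does not stand in the way on the protocol's own criterion, since 3,070 and 4,273 are both below about 14,234. That criterion limits overfitting. It does not give power or precision for interactions, and those rest largely on the roughly 4,745 withdrawn patients across three arms.

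**What to change.** - Pre-list a small set of arm-by-covariate interactions, for example with sex, age, epilepsy type and baseline seizure frequency, and penalise them. Alternatively, fit arm-specific models with arm-specific covariate effects; separate baseline hazards alone would leave the order at any given time the same for every patient.
- Leave the arm terms unpenalised.
- Retain every confounder from the causal graph, by forcing it into the model or by fitting with the Aim 1 weights, and state which.
- Recompute the Table 1 minimum for the full parameter count, including multi-category covariates and interactions.
- In the CPRD validation, report calibration separately by arm.

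If interactions are not added, state in the protocol and on the tool that it gives individual absolute risks under one common ranking of the alternatives.

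The cost is revised model wording, a larger stated minimum sample and some extra analysis. Individual predictions become less precise, which is the reason to keep the interactions few and penalised.
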